### 2.2 Study design

This study will test the hypothesis that COVID-19 infection promotes systemic endothelial dysfunction, impairing NVC responses and promoting white matter damage, contributing to the progression of MCI to dementia. To test this hypothesis, we will prospectively follow patients, who are diagnosed with MCI, with or without history of SARS-CoV-2 infection, for 18 months. The timeline for study design and investigative measurements are represented in **Fig 1.** Study participants will be evaluated for eligibility and enrolled through neurology clinics at the University of Oklahoma Health Sciences Center (OUHSC) and Oklahoma City Veterans Affairs (VA) Medical Center (Visit 0). Upon enrollment, patient history, demographic data, standard risk factors for dementia, cognitive status and WMH status (MRI scan) will be recorded. Blood collection, cognitive tests (NIH-toolbox, *n-*back), and baseline physiologic assessments for peripheral endothelial function (flow-mediated dilation [FMD], laser speckle contrast imaging [LSCI]) and NVC responses (functional near-infrared spectroscopy [fNIRS], dynamic retinal vessel analysis [DVA]) will be conducted at the OUHSC Translational Geroscience Laboratory (Visit 1). Study participants will undergo semi-annual clinical neurologic evaluations as a part of standard care. In addition to COVID-19 status since enrollment (e.g., PCR+/-, symptoms), progression from MCI to dementia will be assessed by the clinical neurology team with final adjudication made through consensus management conferences. Repeat of all physiological assessments, cognitive tests, and serum collection will be performed at month 18 (Visit 2), and the second MRI scan will be performed. If some participants decide to terminate their participation in the study for any reason, they will be invited to an early termination visit, which will include the same evaluations as in Visit 2.

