■ Aim 1 variables will be used to address whether history of SARS-CoV-2 infection impairs systemic endothelial function and NVC response in patients with MCI. Variables included in this Aim are: NVC, band-limited power of brain waves, retinal arteriolar function, microvascular endothelial function, macrovascular endothelial function, endothelial dysfunction biomarkers, pro-inflammatory cytokine level, antioxidant capacity, COVID-19 status, SARS-CoV-2 variants, time since infection, and vaccination history.■ Aim 2 variables will be used to address whether MCI patients with history of COVID-19 have impaired fluid cognitive function compared to MCI patients with no COVID-19 history. Variables included in this Aim are: *n*-back working memory performance, fluid intelligence, COVID-19 status, SARS-CoV-2 variants, time since infection, and vaccination history.■ Aim 3 variables will be used to address whether history of COVID-19 in patients with previously diagnosed MCI contributes to progression to dementia, and whether impaired NVC associates with increased progression to dementia. Variables included in this Aim are: NVC, retinal arteriolar function, band limited power of brain waves, COVID-19 status, SARS-CoV-2 variants, time since infection, vaccination history, and progression of MCI to dementia.■ Aim 4 variables will be used to address whether history of COVID-19 in MCI contributes to increased burden of WMH, and whether elevated level of WMH burden contributes to increased progression of MCI to dementia. Variables included in this Aim are: Fazekas scale, COVID-19 status, SARS-CoV-2 variants, time since infection, vaccination history, and progression of MCI to dementia.

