## 4. Statistical analysis

### 4.1 Cross-sectional data analysis

Upon testing for normality of continuous data, independent t-test or Mann-Whitney *U* Test will be used for group comparison (COVID+ vs COVID-) and Chi-square or Fisher’s exact test for group comparison of categorical variables. Effect size will be calculated for all within and between group analyses. For **primary outcome** analysis, testing whether COVID-19 impairs NVC responses in MCI patients, fNIRS data will be analyzed using a pipeline based on General Linear Model (GLM) approach created using the Brain AnalyzIR toolbox. At the first (subject) level, regression (β) coefficients characterize NVC response and will be estimated for channels of interest in the prefrontal cortex across all n-back blocks and chromophores (HbO and HbR). At the second (group) level the GLM treats COVID status as an independent categorical factor, while the n-back block as a repeated measures factor and yields corresponding *t*-contrasts comparing NVC response within and between groups. We will test whether demographic variables, COVID-19 variants, duration of COVID-19 and vaccination influences the primary outcome through linear regression. Moreover, we will create a multivariate model using β coefficients, generated from the fNIRS pipeline, to determine whether COVID-19 predicts impairment in NVC in MCI patients. Univariate analyses of factors that may contribute to NVC impairment (i.e., age, sex, baseline structural MRI abnormalities) will be conducted, and analyses with a p value of <0.2 will be included in the multivariate model. **Secondary outcome** measures (i.e., FMD, LSCI, EEG, DVA, NIH Toolbox, circulating factors) will be compared between groups. Additionally, we will determine whether history of COVID-19 contributes to impairment in functional cognitive measures (i.e., n-back, NIH Toolbox) by multiple and simple linear regression. For **exploratory analyses**, we will determine whether group (COVID+ vs COVID-) alters the relation between NVC and peripheral, cognitive, and structural measures through multiple regression. Correlations for these variables will be performed within groups to determine strength of relationship with NVC.

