### 4.2 Longitudinal data analysis

Continuous data will be analyzed by 2-way ANOVA and categorical with Chi-square or Fisher’s exact test for within and between groups (COVID+ vs COVID-) comparison. Effect size will be calculated for all within and between group analyses. For **primary outcome** analysis, we will determine whether COVID-19 related impairment in NVC and increases in WMH burden contributes to progression to dementia. Progression to dementia within and between groups will be analyzed and multivariate analysis will be conducted to determine the effect of COVID-19, NVC (i.e., fNIRS), change in WMH burden, and interaction between group (COVID+, COVID-) and NVC and WMH burden on progression to dementia. **Secondary outcome** measures (i.e., FMD, LSCI, EEG, DVA, NIH Toolbox, circulating factors) will be compared within and between groups. Demographic variables, COVID-19 variants, duration of COVID-19 and vaccination will be assessed as factors for progression to dementia through logistic regression. **Exploratory analyses** will include univariate analysis of all demographics, physiologic, cognitive, and structural variables, and their effect on progression to dementia. All values with a p value <0.2 will be included in a multivariate model to assess their contribution to progression to dementia. We expect that several variables will have p value <0.2; therefore, we will conduct dimensionality reduction before adding into the model to assess variables which have strongest correlation with principal components. The limitation for the multivariate model will be sample size, however this is not a primary outcome measure and is used to generate new hypotheses to test in future studies.

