As with any longitudinal observational study, maintaining contact with all participants can be difficult, particularly when dealing with extended follow-up periods. Losing contact with a significant number of patients can result in biased outcomes, especially if the reason for loss to follow-up is related to the risk factor or outcome of interest—dementia. Additionally, due to the presence of confounding variables, observational studies have limited capacity to establish causation from the observed association between COVID-19 infection and conversion rate to dementia. Therefore, it is necessary to distinguish the effects of COVID-19 from other factors such as medical history, comorbidities, hospital interventions, and critical care status. In conclusion, cognitive impairment is linked to COVID-19, and it is a major contributor small vessel cerebrovascular complication. Therefore, we will elucidate a mechanism for how history of COVID-19 affects cognitive function and can pave the way for future therapeutic interventions targeting neurovascular uncoupling as a prominent feature in the conversion to dementia.

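### The primary progression model and the group-level fNIRS model list no baseline confounders, so in this non-randomised cohort their estimates are open to confounding

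*Protocol article*

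**What the plan says.** **Design.** Section 2.2 describes an observational cohort: "we will prospectively follow patients, who are diagnosed with MCI, with or without history of SARS-CoV-2 infection, for 18 months".

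**Progression to dementia (4.2, primary).** "multivariate analysis will be conducted to determine the effect of COVID-19, NVC (i.e., fNIRS), change in WMH burden, and interaction between group", the interactions being with NVC and WMH burden. Another sentence adds: "Demographic variables, COVID-19 variants, duration of COVID-19 and vaccination will be assessed as factors for progression to dementia through logistic regression". A wider progression model, built from variables with univariate p<0.2 and then reduced in dimension, is placed under exploratory analyses and is said not to be a primary outcome measure.

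**NVC (4.1, primary).** The second-level fNIRS model has COVID status as group factor and n-back block as repeated factor. Linear regression tests whether demographic variables, variant, duration and vaccination influence the outcome. A further multivariate model asks whether COVID-19 predicts NVC impairment. Its covariates come from a screen in which each candidate is tested alone; those named are age, sex and structural abnormalities on the baseline MRI. The entry rule reads: "analyses with a p value of <0.2 will be included in the multivariate model".

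**Confounding.** Section 5 states that "it is necessary to distinguish the effects of COVID-19 from other factors such as medical history, comorbidities", among others. Section 1 names diabetes, hypertension and atherosclerosis as raising conversion to dementia. Section 5 names aging, diabetes, hypertension, dyslipidemia and obesity as impairing NVC. Table 1 lists age, sex, education, MoCA, comorbidities and Fazekas grade among the study variables.

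**The concern.** Infected and uninfected patients may differ in age, education, severity at diagnosis and vascular disease. By the protocol's own account, several of these also drive NVC or dementia. A model without them attributes to COVID-19, NVC or WMH change whatever part of the difference they cause.

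Change in WMH does not fill the gap. It is a hypothesised step on the path from infection to dementia, so including it does not adjust for the vascular burden a patient had at the start.

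At stake is the main claim. Section 1 sets out to establish a mechanistic link between COVID-19 and progression, and the primary models carry that claim. An adjustment set chosen once the data have been seen would not be prespecified.

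**Working it through.** **1. Stated models against the protocol's own confounders**

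| Factor | 4.2 primary progression model | 4.1 group-level fNIRS model | 4.1 multivariate NVC model |
|---|---|---|---|
| Age, sex | not listed | not listed | only if p<0.2 |
| Education | not listed | not listed | not named |
| Baseline cognition (MoCA) | not listed | not listed | not named |
| Baseline WMH | not listed (change only) | not listed | baseline MRI abnormalities, only if p<0.2 |
| Hypertension, diabetes | not listed | not listed | not named |

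**2. The plan's own figure.** Section 2.4 gives progression of 10/18 (55.6%) against 23/100 (23%), p = 0.011. A Yates-corrected chi-square gives p = 0.0108, which agrees. The crude odds ratio is (10 × 77)/(8 × 23) = 4.18, with no adjustment.

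**3. What an omitted factor could do to progression.** Assumptions: no true COVID effect, control risk 23% (section 2.4), 100 per group, two-sided 5%, one binary factor with a given odds ratio. The factor prevalences and odds ratios are not in the document.

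Let c be the risk without the factor and a = OR·c/(1 + (OR − 1)c) the risk with it. Solve π₀a + (1 − π₀)c = 0.23 for c, where π₀ is the control prevalence. The infected-group risk is then π₁a + (1 − π₁)c.

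For π₁ = 0.60, π₀ = 0.40, OR = 3: c = 0.151, a = 0.348, infected risk 0.6 × 0.348 + 0.4 × 0.151 = 0.269. The false odds ratio is (0.269/0.731)/(0.23/0.77) = 1.23. The standard error is √(0.269 × 0.731/100 + 0.23 × 0.77/100) = 0.061, and the rejection rate about 10%.

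| Prevalence, infected vs not | Factor OR | False OR | False positives |
|---|---|---|---|
| 50% vs 40% | 2 | 1.07 | 5.5% |
| 60% vs 40% | 3 | 1.23 | about 10% |
| 70% vs 30% | 4 | 1.69 | about 39% |

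A simulation with a continuous factor (172 patients, 1:1, OR 2 per SD, 800 data sets) agrees in scale. A 0.3 SD imbalance gave a false odds ratio of 1.20 and 7.8% rejection (6.1% adjusted). A 0.5 SD imbalance gave 1.39 and 15.6% (5.4% adjusted). Both checks test COVID status alone, not the full model with NVC, WMH change and interactions.

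**4. NVC and the p<0.2 screen.** Simulation with n = 200, no COVID effect, five weak factors (slope 0.1 each), 2000 data sets; slopes and imbalances are assumed.

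| Analysis | Type I error, 0.3 SD | Type I error, 0.4 SD |
|---|---|---|
| No covariates | 17.9% | 28.7% |
| p<0.2 screen, all five candidates | 5.4% | 4.8% |
| Fixed adjustment for all five | 5.4% | 4.7% |

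The screen dropped 36–40% of the real factors but did not raise the error here. If only three of the five are candidates, screened error is 7.6–8.6%, and 12–18% at slope 0.2. That variant is an assumption, prompted by section 4.1 not naming comorbidity or baseline cognition.

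**5. Events available for adjustment** (rates from section 2.4)

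- High: 200 evaluable, 1:1: 100 × 0.556 + 100 × 0.23 = 78.6 events.
- Low: 200 × 0.90 × 0.95 = 171 evaluable (10% dropout; 5% deaths, an assumed reading of section 2.4). At the earlier cohort's mix, 171 × 33/118 = 47.8 events.

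| Model | Parameters | Events per parameter |
|---|---|---|
| As listed (three main effects, two interactions) | 5 | 9.6–15.7 |
| Plus six covariates | 11 | 4.3–7.1 |
| Plus six covariates, interactions removed | 9 | 5.3–8.7 |

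This counts NVC, WMH and each covariate as one parameter. Separate periventricular and deep Fazekas grades would add more.

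**The case against.** The best defence is that the sentence in 4.2 names the effects of interest and does not say covariates are excluded, and that an article may leave the exact set to a fuller document. The regression of demographic variables may also be wider than it looks: Table 1 labels age, sex, education, MoCA and comorbidities alike as demographic, and 4.2 does not say whether COVID status is in that regression. Some protection exists. Section 2.6 excludes uncontrolled chronic conditions, 2.10 requires common age-related conditions to be pharmacologically controlled, and 3.1.2 and 3.2.1 compare baseline WMH and blood pressure between groups. Section 5 concedes the limits of observational data.

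This reduces the concern but does not remove it. The article states the model terms and places the wider progression model outside the primary analysis. The other regressions assess variables as factors in their own right, not as adjustment of the COVID effect. Controlled hypertension and diabetes remain in the cohort, and checking for imbalance is not adjusting for it.

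A reader might also infer more than the document supports:

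- *The COVID effect is confounded.* No group imbalance is reported, so only openness to confounding can be claimed.
- *The p<0.2 screen inflates the error.* It did not when every confounder was a candidate. The 18–29% figures belong to an analysis without covariates, not to the screened NVC model.
- *The Aim 3 list in section 2.9 shows that confounders were left out.* These lists are not model specifications: Aim 3 omits WMH, which the 4.2 model includes, and Aim 1 omits age and sex, which 4.1 names as candidates.
- *Patients already at Fazekas 3 are misclassified as unchanged.* The document does not define how change is scored, and the effect is unquantified.

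**Conclusion.** The point stands as a should-fix. As written, the primary progression model and the group-level fNIRS model contain no baseline confounder, although the protocol itself says such factors must be separated from COVID-19. The direction and size of any bias are unknown. Under the assumed single-factor inputs, the false odds ratio for progression runs from 1.07 to 1.69, with 5.5% to 39% false positives; the upper end needs a strong factor and a large imbalance. None of these settings reaches the crude odds ratio of 4.18 in the earlier cohort, but they could matter for a more modest true effect.

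The missing forced adjustment is the main point. The p<0.2 rule is secondary: its weakness is that baseline cognition and comorbidity are not named as candidates. The event counts assume that the section 2.4 rates hold.

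**What to change.** Prespecify one short adjustment set from variables already in Table 1: age, sex, education, baseline MoCA, baseline Fazekas grade, and hypertension/diabetes. Force it into both the 4.1 group-level NVC model and the 4.2 primary progression model, whatever the univariate p-values. Keep the p<0.2 screen for additional or exploratory covariates only.

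State when baseline MoCA is measured, because Table 1 does not. A score taken after infection could itself reflect COVID-19, so a score from MCI diagnosis is preferable where one exists. The index MRI does not have this problem, since section 2.7 dates it before the pandemic. Time since MCI diagnosis would be a reasonable addition, but Table 1 does not list it and it would have to be taken from records.

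The cost is more than wording. Eleven parameters leave about 4 to 7 events each, so make the interactions secondary, or use a propensity score or a penalised fit with the same set. Removing the interactions alone raises this only to about 5 to 9. No new measurement is needed for the core set, provided a suitable MoCA score is on record.

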## 5. Discussion

Given the high burden of COVID-19 infection and increasing number of elderly individuals in our population, this study has the potential to shed light on the burden and predictors of cognitive decline and dementia in our setting. COVID-19 patients are prone to develop cerebrovascular complications, particularly among older individuals and those with age-related conditions [22]. Although the underlying etiology of cerebrovascular accidents in this patient population are not yet fully understood, research suggest that the SARS-CoV-2 virus may have a systemic impact, increasing age-related chronic elevation in thromboinflammation and reactive oxygen species (ROS) levels, which can have detrimental effects on the vasculature [93,97–99,105,106]. Previous studies have shown that impairment of NVC and endothelial function play a significant role in the pathogenesis of cognitive decline and dementia [43] and there is a growing body of evidence linking COVID-19 with endothelial dysfunction [106,107]. Cognitive impairment has been identified as a significant complication following recovery of acute COVID-19 [108]. Additionally, COVID-19-induced increases in the burden of WMH have been linked to an increased risk of dementia in patients with MCI [21]. We predict that COVID-19 infection will promote systemic endothelial dysfunction, impair NVC responses and promote white matter damage, contributing to the progression of MCI to dementia. Moreover, we expect that COVID-19 infection will lead to an elevation in circulating reactive oxygen species (ROS), proinflammatory cytokines, and biomarkers of endothelial dysfunction. Elevation in these molecules have a deleterious effect on the vasculature [91] and is implicated in the development of cognitive decline and dementia [103,109]. Furthermore, evidence suggests that following recovery of COVID-19 infection, there is a prolonged thromboinflammatory response, in part, mediated by systemic endothelial dysfunction [106].

Conditions known to cause elevations in oxidative stress and chronic inflammation (i.e., aging [110], diabetes [111], hypertension [112], dyslipidemia [113], obesity [114]) have impaired cerebromicrovascular function [32,115,116] (e.g., endothelial nitric oxide synthase uncoupling, peroxynitrite formation) and contributes to a decreased NVC response, resulting in cognitive dysfunction [16,40,41,117,118]. However, in preclinical and clinical studies, the NVC response can be rescued, improving cognitive outcomes in aging and age-related diseases by antioxidant rich treatments [33,34,37–39]. Hence, as elevations in ROS has been shown in recovered COVID-19 patients and chronically elevated oxidative stress may play a large role in persistent endothelial dysfunction [105] and long-COVID symptoms [119], such as cognitive impairment or “brain fog”, the use of antioxidant treatments may be of interest to rescue a potentially dysregulated NVC response. A recent systematic review has outlined the beneficial use of antioxidants (i.e., vitamins C, D, selenium and zinc) thus far for the treatment of COVID-19 complications [120], and vitamin C, specifically, has shown endothelial protective effects [106]. In addition, Tocilizumab, a humanized anti-IL-6 receptor antibody, has shown beneficial endothelial effects [121], potentially due to glycocalyx thickening, reducing the high inflammatory and oxidative stress burden seen in COVID-19 [106]. While antioxidant treatments have been trialed for acute COVID-19 conditions, albeit limited, the use of treatments with beneficial effects on oxidative stress levels is recovered COVID-19 patients are scarce.

Nicotinamide adenine dinucleotide (NAD+) supplementation is of particular interest in the mitigation of long-term COVID-19 symptoms. Low NAD+ levels are implicated in the pathogenesis of age-related diseases associated with poor COVID-19 outcomes. Hence elevating NAD+ levels may decrease inflammation and high levels of ROS, promoting anti-viral defense, and potentially alleviating long-term COVID-19 complications [122,123]. Nicotinamide riboside (NR) is an NAD^+^ precursor and administration of NR, or other precursors (nicotinamide mononucleotide [NMN]) restored NAD+ levels in aged cerebromicrovascular endothelial cells (CMVEC), reduced CMVEC mitochondrial ROS, and rescued NVC responses in old mice, associating with improved cognitive performance [38]. NAD+ is a rate limiting co-substrate for sirtuin enzymes, which are involved in maintaining proper mitochondrial function (e.g., mitophagy, biogenesis) [124], and protect the cell from aberrant ROS production [125]. In addition, pharmacological SIRT1 activator SS-31 improved cerebromicrovascular endothelial function, NVC responses, and cognitive function, further indicating a role for NAD+ and NAD+ intermediates to be translated from preclinical to clinical trials [39]. NAD+ bioavailability decreases as we age and during viral infections, in part due to upregulation of NAD+ consuming enzymes, such as poly(ADP-ribose) polymerase 1 (PARP1) [122], which interacts with NF-kB signaling, precipitating further chronic inflammation and oxidative stress [91]. Moreover, we are currently conducting a clinical trial to elucidate the effects of NR supplementation on systemic endothelial function, NVC responses, and cognition in healthy aging individuals (Effect of NAD supplementation on brain vascular health in aging) with the anticipation of identifying cognitive and vascular benefits reported in preclinical trails. Following this, NR supplementation may prove beneficial in future trials targeting cerebromicrovascular endothelial dysfunction in age related diseases and conditions known to deplete NAD+. NAD+ intermediate supplements may provide relief from persistent COVID-19 related cognitive dysfunction and need to be investigated as a therapeutic to target the NVC mechanism.

As with any longitudinal observational study, maintaining contact with all participants can be difficult, particularly when dealing with extended follow-up periods. Losing contact with a significant number of patients can result in biased outcomes, especially if the reason for loss to follow-up is related to the risk factor or outcome of interest—dementia. Additionally, due to the presence of confounding variables, observational studies have limited capacity to establish causation from the observed association between COVID-19 infection and conversion rate to dementia. Therefore, it is necessary to distinguish the effects of COVID-19 from other factors such as medical history, comorbidities, hospital interventions, and critical care status. In conclusion, cognitive impairment is linked to COVID-19, and it is a major contributor small vessel cerebrovascular complication. Therefore, we will elucidate a mechanism for how history of COVID-19 affects cognitive function and can pave the way for future therapeutic interventions targeting neurovascular uncoupling as a prominent feature in the conversion to dementia.
